**Table 4: Minimum sample sizes by effect sizes, power and number of measurements**

| **Effect**  **size** | **Minimum Sample size per Group (2 tailed test, alpha=0.05, Correlation between repeated measurements=0.2)** | | | |
| --- | --- | --- | --- | --- |
| 80% Power  Time Points  1 2 3 | 85% Power  Time Points  1 2 3 | 90% Power  Time Points  1 2 3 | 95% Power  Time Points  1 2 3 |
| 0.2 | 393 237 185 | 450 271 211 | 526 317 247 | 651 391 305 |
| 0.3 | 175 106 83 | 201 121 95 | 234 142 110 | 290 175 136 |
| 0.4 | 99 60 47 | 113 69 54 | 132 80 63 | 163 99 77 |
| 0.5 | 64 39 31 | 73 45 35 | 85 52 41 | 105 64 50 |

**D.1.5. Recruitment of study subjects**: *(revised)*

*The power calculations dictate that a* minimum of 676 mother-child pairs should complete the study. We expect a 15% loss to follow up during pregnancy and a further 20% loss in infancy, and therefore need to recruit at least 994 pregnancies. *These estimates are conservative and include losses due to deaths and migrations out of the study area. All efforts however will be made to keep losses to a minimum. Attendance at routine prenatal and postnatal visits is already high in our study hospital and in addition we will be providing incentives to encourage participation.* Recent data indicate that IMSS General Hospital I has approximately 250 births/month, of which ~60% are predominantly breastfed until 3 months of age. The proportion of pregnancies that are high risk and therefore ineligible for inclusion is about 10%. Based on the above data, we expect to recruit at least 100 eligible pregnancies per month and therefore to complete recruitment in 10 months. The 30% subsample of mother-infant pairs for biochemical determinations will be selected at random.

**D.1.6. Time line:** *(revised)*

The total duration of this project is *four* years and the time line for the main activities is shown in Figure 3. Activities related to the development of the protocol, pre-testing and finalizing questionnaires, hiring and training of all study staff will be carried out in the first year. The total duration of data collection will be about 32 months. Recruitment of subjects for the intervention trial will begin in the middle of the first year and will be completed in 10 months (see recruitment). The total duration of follow-up is 23 months (5 months of pregnancy and 18 months during early childhood) for each mother-child pair and therefore, all data collection will be completed early in the fourth year. Data entry and cleaning will be carried out in an on-going fashion. All lab estimations will be carried out during years 2-4. Data analysis will be conducted in the last two years and the preparation and submission of manuscripts for publication will be done in the final year.

**D.2. Data collection** *(revised)*

**D.2.1. Field operations and field team**

The details of the protocol for data collection during the prenatal and post-natal follow-up periods for each mother-child pair in the study are shown in Table 5. The study team in charge of data collection and the intervention trial will comprise of a study director who will be a physician based at IMSS General Hospital I and will report directly to the study investigators at INSP, Cuernavaca as shown in Figure 4. He/she will be assisted by area supervisors who will oversee data collection and ensure data quality. All prenatal care will be provided by trained hospital staff.

A hotline will be maintained for all study subjects to contact the study team. In terms of data collection, if we recruit about 100 pregnancies per month, we expect to have approximately 85 births per mo and approximately 70 infants/mo at 18 months of age. A team of 5-8 field workers will be hired to visit all pregnant women at home on a

**Figure 4: Organization Structure for Field Operations**

**Study Investigator ([name])**

**Hospital Staff**

*Prenatal care and Delivery*

**Team I** (8 FW)

*Supplement Distribution*

**Team II** (*5 nurses*)

*Anthropometry*

*Dietary intakes*

*SES, Obstetric history*

*Blood samples*

*Breast-milk samples*

**Team III** *(*3 PSY)

*Maternal Intelligence Neurodevelopment*

**Team IV** (2 SW)

*Home environment*

**Field Director ([name])**

***Supervisor I (Physician) Supervisor II (Nutritionist) Supervisor III (Psyschologist)***

*FW – Field Workers; PSY – Pyschologists; SW- Social Workers*

Table 5: Details of data collection during prenatal and postnatal follow-up

|  | Prenatal | | | | **Birth** | | **Post-partum (mo)** | | | | | | | | | | | |
| --- | --- | --- | --- | --- | --- | --- | --- | --- | --- | --- | --- | --- | --- | --- | --- | --- | --- | --- |
|  | Baseline (20-24 wks gestation) | | **Intervention** | |  | | **1** | | **3** | | **6** | | **9** | | **12** | | **18** | |
| Sociodemographic characteristics | **X** | |  | |  | |  | |  | |  | |  | |  | |  | |
| Obstetric History | **X** | |  | |  | |  | |  | |  | |  | |  | |  | |
| Supplement consumption |  | | **X** | |  | |  | |  | |  | |  | |  | |  | |
| *Maternal diet* | **X** | |  | |  | |  | | **X** | | *X* | |  | |  | |  | |
| Maternal anthropometry | **X** | |  | |  | |  | | **X** | |  | |  | |  | |  | |
| Maternal Weight | **X** | | **X** | |  | |  | | **X** | |  | |  | |  | |  | |
| Maternal PUFA status | **X** | |  | | **X** | | **X** | | **X** | |  | |  | |  | |  | |
| Gestational age and birth outcomes |  | |  | | **X** | |  | |  | |  | |  | |  | |  | |
| Infant anthropometry |  | |  | | **X** | | **X** | | **X** | | **X** | | **X** | | **X** | | **X** | |
| Infant PUFA status |  | |  | | **X** | |  | | **X** | |  | |  | | **X** | | **X** | |
| Apgar & NBAS scores |  | |  | | **X** | | **X** | |  | |  | |  | |  | |  | |
| *Visual and Brainstem Auditory Evoked Potentials* |  | |  | |  | | *X* | |  | |  | |  | |  | |  | |
| Visual recognition memory and visual attention |  | |  | |  | |  | |  | | **X** | |  | | **X** | |  | |
| Global mental and motor development (Bayley) |  | |  | |  | |  | |  | | **X** | |  | | **X** | | **X** | |
| Infant Diet | |  | |  | |  | | X | | **X** | | **X** | | **X** | | **X** | | **X** |
| Breast milk PUFA | |  | |  | |  | | **X** | | **X** | |  | |  | |  | |  |
| *Home environment* | |  | |  | |  | |  | |  | | **X** | |  | | **X** | | *X* |
| Maternal Intelligence | | **X** | |  | |  | |  | |  | |  | |  | |  | |  |

weekly basis to distribute supplements and monitor compliance. *These workers will have a minimum qualification of having completed high school and will be trained to provide referrals for health care if required.* We expect about 100 - 400 women in the study per month and each worker will cover approximately 40-50 women. A team of 4*-5* trained nurses will obtain all baseline measurements (anthropometry, sociodemographic characteristics and obstetric history, diet, blood samples) at recruitment. They will also collect similar data for infants as well as blood and breast milk samples from mothers and *assist in measuring visual and auditory evoked potentials* and monitoring the birth outcomes to be collected as part of routine hospital procedures. All infant measurements will be done at the study headquarters in the IMSS General Hospital I. Mothers will be scheduled to bring their infants at 1, 3, 6, 9, 12 and 18 months, at which time growth and neurodevelopment outcomes will be measured. The total contact time per mother-infant pair is expected to range from 1-2 hours per visit of which the contact time for the infant ranges from 30 minutes at 9 months to 90 and 110 minutes at 12 and 18 months of age, respectively. The date of each assessment will be calculated based on birth date, plus or minus 7 days. A team of 3 trained psychologists will conduct all neurodevelopment and psychological measurements at the study headquarters. These include maternal intelligence at recruitment and the infant neurodevelopment outcomes, namely Neonatal Behavioural Assessment Scale (NBAS), Fagan and Bayley tests of motor and mental development (see section D. 2.2.1. for details). Approximately 4-5 infants will be scheduled daily (6 days a week) to be measured by the study nurse and psychologist. *Finally, two trained social workers will collect data on home environment during home visits at 6 and 12 months of age and at the study headquarters at 18 month of age.* Other study personnel will include an assistant who will coordinate all appointments and follow-up for data collection. Data entry operators (2) and lab assistants (1) will assist in data entry and cleaning and handling and analysis of biological samples at INSP.

**D.2.2. Measurement of Key Outcomes**

#### D.2.2.1. Infant Neurodevelopment *(revised)*

#### Neurodevelopment will be assessed at birth, and at 1, 6, 12 and 18 months of age for all infants born to women who participated in the intervention trial during pregnancy.

***a. Apgar and Neonatal Behavioral Assessment Scale (NBAS):***The infant’s condition shortly after delivery will be evaluated using the **Apgar Score**[[193]](#endnote-193), a test routinely conducted at 1, 5 and 10 minutes post delivery to assess the infant’s status in five areas: heart rate, respiration, tone, reflex, and color. Scores for the individual areas range from 0 to 2, with a total number of 10 points possible. Total scores of 7 and above indicate the child is in good condition and at low risk for needing immediate medical attention. Infants whose 5-minute score remains low (0-3) are at risk for lasting problems, including neurological damage such as cerebral palsy or mental retardation[[194]](#endnote-194). The **Neonatal Behavioral Assessment Scale** (NBAS)[[195]](#endnote-195) will be administered to infants 48 hours after birth and at 1 month of age. The NBAS yields information on both the infant’s behavior (responses to certain stimuli -28 items), and reflexes (18 items), with supplementary information provided on qualities such as alertness, irritability, and endurance. The NBAS takes approximately 20-30 minutes to administer and will be done by trained examiners with some background in theories of child development and/or or experience with babies and neonates.

***b. Global mental and motor development***: Mental and motor development will be assessed at 6, 12 and 18 months of age using **the Bayley Scales of Infant Development-II** (BSID-II)Error: Reference source not found, which have been used in other studies of the

relationship between infant LCPUFA status and behavioral outcomes in humans[[196]](#endnote-196). The BSID consist of 3 scales: the Mental Scale (MDI), the Psychomotor Scale (PDI), and the Behavior Rating Scale *(see Appendix III for English and Spanish versions used in previous studies*). The MDI evaluates memory, habituation, problem solving, early number concepts, generalization, classification, vocalizations, and language. The PDI evaluates control of the gross muscle groups including movements associated with rolling, crawling and creeping, sitting, standing, walking, running and jumping. The PDI also tests fine motor manipulations involved in prehension, adaptive use of writing implements, and imitation of hand movements. The Behavioral Rating Scale assesses the child's behavior during the testing situation, which facilitates interpretation of the Mental and Motor Scales. The three scales are considered complementary, and each makes a unique contribution to the evaluation of the child. Each evaluation begins by administrating the recommended starting item from the age-appropriate item set. The infant’s raw summary scores on the Mental and Motor Scales are computed by adding the total number of items for which the child receives credit on each scale and all items below the basal item. The raw scores are then translated into Mental and Psychomotor Development Indices that are standardized to a mean of 100 ± 15. The average reliability is expected to range between 0.84 – 0.92 for the different components in children aged 6-18 mos. Interscorer agreement is 0.96 and 0.75 for the mental and motor scales, respectivelyError: Reference source not found. The BSID also provides guidelines for classification of these standardized scores into the categories of “Accelerated Performance” (115+), “Within Normal Limits” (85-114), “Mildly Delayed Performance” (70-84), and “Significantly Delayed Performance” (69 and below). Previous work has shown that the total duration of these tests increases with age and ranges between 25- 40 minutes per contact.

***c. Visual and Brainstem Auditory Evoked potentials, visual recognition memory and visual attention****: Since BSID assesses global development, more specific neurophysiological measures are required: visual evoked potentials (VEP), brainstem auditory evoked potentials (BAEP), visual recognition memory and visual attention.*

***VEP and BAEP*** *will be assessed in infants at 1 month of age at the hospital by a trained nurse and neurologist. VEP will be elicited by a light-emiting diode (LED) photostimulator fitted in goggles, without dark adaptation; pupils will not be dilated; the stimuli will be presented at 0.5/s, delivering an output intensity of 1500 cd/m2. VEPs will be recorded from an active electrode at the inion (Oz) referenced to a mid-frontal electrode (Fz). At least 2 averages of 64 trials each will be collected**[[197]](#endnote-197). For BAEP, surface gold-cup electrodes, 4mm in diameter, attached with paste and tape will be used in both ears for stimulation and for recording. Electrode impedances will be below 5 k. Electrical activity will be evoked and recorded on a Nicolet Spirit. The click stimulation will be presented monoaurally at 70 dB hearing level and repeated 3000 times. The auditory stimulus is constant polarity rarefaction click delivered at 10/s via pediatric headphones. BAEPs will be recorded between the vertex (Cz) and the mastoid ipsilateral to the stimulated ear (A1 or A2)Error: Reference source not found. The total duration of these assessments will be 60 minutes and will not cause any discomfort to the infants.*

*Visual recognition memory (novelty preference) and visual attention (look duration)**will be assessed at 6 and 12 months using* ***the Fagan Test of Infant Intelligence (FTII)****[[198]](#endnote-198). The FTII is a standardized, paired-comparison test, was developed to identify infants at risk for cognitive deficits[[199]](#endnote-199) and has been shown to be predictive of later performance on standardized intelligence tests[[200]](#endnote-200),[[201]](#endnote-201),[[202]](#endnote-202). In this test, the infant is seated on his or her mother's lap in front of a stage and is presented with pictures of faces. The complete test uses a series of 10 familiarizations, each of which is followed by a paired-comparison trial in which the novel stimulus is presented first on one side and then on the other. Tasks include “familiarization”, “duration of each look”, and “visual attention to a novel stimuli“. Preference for the novel picture, expressed as `percentage fixation preference', shows that the two pictures are discriminable, and also indicates that the infant can recognize one of the pictures as familiar. The final value is called the `novelty score'. This score is the length of fixation time during the test phase devoted to the novel picture divided by the total fixation time to both the novel and familiar picture, multiplied by 100. The required interval for familiarization decreases with increasing age, as does the time allowed for each paired-comparison test.*

#### D.2.2.2. Maternal and Child Anthropometry (*revised)*: Maternal anthropometry will be obtained at recruitment and will include height, weight, mid-arm circumference, and triceps and subscapular skinfold thickness using standard procedures**[[203]](#endnote-203)** by trained workers. Details of maternal weight gain during pregnancy will be obtained from medical records. Weights will be recorded to the nearest 0.1 kg and heights to the nearest 0.5 cm. Length, weight and head circumference of the infants will be measured at birth and at 1, 3, 6, 9, 12 and 18 months of age using standard procedures. Data collectors will be trained in anthropometric techniques, and regular standardizations will be carried out. Measurement of accuracy and precision for all anthropometric measurements will be done using methods recommended by Lohman et al (1988)Error: Reference source not found. The scale will be calibrated twice daily with a known reference weight. All data collection will be done at the study headquarters and will be obtained in duplicate by the same data collector. Children will be weighed using a pediatric weighing scale with a precision of 10 g. Infants will be weighed without clothing at birth and with a minimum of clothing (e.g., undershirt, underpants or dry diaper) for subsequent measurements. The weight of clothing will be adjusted for using a second set of clothing. Recumbent length will be measured using a baby-board (UNICEF, Copenhagen, Denmark). Measurements will be read to the nearest 0.1 cm. Weight-for-age and length-for-age z scores will be calculated using the National Center for Health Statistics reference data**[[204]](#endnote-204)**. Head circumference will be measured at the largest occipitofrontal circumference to the nearest 0.1 cm with a non-stretchable tape.

D.2.2.3. Gestational Age and Birth Outcomes *(revised):* Details of birth outcomes (type of delivery, sex, livebirth, etc) will be obtained from hospital records and will be verified by interview in a 10% sub-sample. Gestational age will be determined at birth using Ballard’s method[[205]](#endnote-205).

D.2.2.4. Long Chain Polyunsaturated Fatty Acid Status (Maternal and Infant): *(revised)*

*Fatty acid composition of plasma phospholipids and RBC membrane phospholipids are appropriate markers of recent intake because they respond rapidly[[206]](#endnote-206). Since the distribution of fatty acids in the phospholipid fraction of plasma is closely related to their distribution in the phospholipids of the RBC membrane, only plasma phospholipid fatty acids (ALA, LA, AA, EPA, and DHA) will be measured in a random 30% subsample of pregnant women and their infants. Maternal blood samples (7 ml) will be obtained by venipuncture at recruitment and at delivery. Neonatal blood samples will be obtained from the umbilical cord vein immediately after delivery. A 5 ml venous blood sample will be obtained at 3, 12 and 18 months of age from infants. All samples will be collected by trained nurses and placed into tubes containing disodium ethylene diamine tetraacetic acid (EDTA). Plasma and RBCs will be separated by centrifugation at 800 g for 10 min at room temperature. Plasma will be frozen in a nitrogen environment and stored at -70° C for later analysis at INSP laboratories. The maternal and infants' plasma total lipids will be extracted using the procedure described by Folch et al[[207]](#endnote-207) and individual and total plasma phospholipid fatty acid methyl esters will be identified using gas-liquid chromatography and expressed both as relative weight (% by wt) and in absolute concentration (mg/L).**Details of lipid extraction, fatty acids methylation and analysis are provided in Appendix V. Details of quality control are described in section D.2.4.*

D.2.2.5. Breast milk PUFA: *(revised)* Breast-milk samples will be collected at 1 and 3 mo post-partum in the same subsample of women who provide venous blood samples. The samples will be taken from a morning feed but not the first one, between 8 and 12 o'clock at the study headquarters. Infants will be allowed to suckle the nipple for a few minutes, and then a breast milk sample (10 ml) will be taken and the feeding continued[[208]](#endnote-208). The samples will be placed in 14 ml glass test tubes, labeled and sealed, and immediately transferred to the freezer at -70°C until analysis. Before storage, the samples will be sonicated and EDTA and butylated hydroxytoluene will be added to a final concentration of 1.85 mg/mL and 75 μg/mL, respectively. Although the amount of fat may change within and between feeds, the proportion of fatty acid remains relatively constant[[209]](#endnote-209),[[210]](#endnote-210). Since breast milk PUFA will be expressed as a % of total fatty acids, complete breast expressions are therefore not required[[211]](#endnote-211). *The fatty acid composition of breastmilk will be analyzed by gas chromatography using standard methods[[212]](#endnote-212),[[213]](#endnote-213) (see Appendix V for details).*

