##### **D.1.1. Study Hypotheses** *(added specific hypothesis 3c)*

The ***central hypothesis*** is that DHA supplementation during pregnancy will improve child growth and development during infancy, and will be tested by conducting a randomized double-blinded placebo-controlled trial in Mexico.

The **specific hypotheses** are:

- 1. Compared to those who receive a placebo, women who receive DHA supplements during the latter half of pregnancy will have **higher DHA concentrations in breast milk and blood** at 1 and 3 months post-partum.

2. Compared to those born to women who receive a placebo, infants born to women who receive DHA supplements during the latter half of pregnancy will have **improved birth outcomes** as follows,

a. Greater birth weight and length and longer gestational age

b. Better neurodevelopmental indicators (Apgar and Neonatal Behavioral Assessment Scale scores)

1. Increased cord blood levels of polyunsaturated fatty acids.
2. Compared to those born to women who receive a placebo, infants born to women who receive DHA supplements during the latter half of pregnancy will have **better growth and neurodevelopment during the first 18 months of life**, namely

a. Increased weight, length and head circumference at 1, 3, 6, 9, 12 and 18 months of age

- 1. Higher Neonatal Behavioral Assessment Scale scores at 1 month of age
  2. *Improved visual and brainstem auditory evoked potentials at 1 month of age*
  3. Improved visual recognition and attention at 6 and 12 months of age
  4. Higher global motor and mental development scores at 6, 12 and 18 months of age
  5. Increased postnatal growth rates independent of birth size
  6. Higher global motor and mental development scores at 18 months of age independent of differences observed at earlier time points (e.g. 6 and 12 months).

1. Compared to those born to women who receive a placebo, infants born to women who receive DHA supplements during the latter half of pregnancy will **higher DHA concentrations in blood** at 3, 12 and 18 months of age.

**D.1.2. Study Design** *(revised)*

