**D.4.2. Analytical Plan:**

The principal outcome variables of interest will be birth outcomes (birth weight, length, maternal and newborn PUFA, neurodevelopment), breast milk PUFA levels, and child growth (weight, length, head circumference) and skinfold thickness) and development (cognitive and motor) at 18 months of age. In addition, weight and length gain from birth to 18 months of age, neurodevelopment at 1, 6 and 12 months, cognitive and motor development at 6 and 12 months and infant PUFA status at 1 and 3 months of age will also be examined. Preliminary descriptive analyses will be done to examine the distribution of the data and check for outliers, following which unadjusted comparisons of mean differences in length and weight and biochemical values will be made using Student's t test. The intervention groups will be compared on several baseline variables to ensure that randomization worked. Chi-square tests will be used to compare categorical variables and Student’s t test will be used to compare normally distributed continuous data. Following this, adjusted comparisons (using co-variance analysis)[[238]](#endnote-238) will be made if controlling for potential confounders is required using linear multiple regression for continuous variables and logistic regression for categorical variables[[239]](#endnote-239). In all cases, results will be presented before and after adjustment for confounding and testing of interactions.

Examples of some of the models for various hypotheses are presented below. For specific hypotheses 2a, using birth weight as the outcome of interest and general linear models regression analysis, we can test the following model:

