***3a. Length (18 mo) = Constant + β 1 (Supplement)+ β2 (Other confounding)* *+ β3  (Supplement * other confounding)***

***3b. Mental development ( 18 mo) = Constant + β1 (Supplement)+ β 2 (Other confounding)* *+***

***β3  (Supplement * other confounding)***

Similar models can be specified to test the hypotheses stated under specific aims 1 & 4, for example that breast milk PUFA levels and infant PUFA status at 1 month of age will be higher in the intervention group compared to ‘control’ group. Mean values of breast milk and blood levels of DHA will be used as the dependent variables. Since some outcomes will also be defined as dichotomous outcomes, some of the hypotheses will also be tested using logistic regression. For example, if the dependent variable for specific hypothesis 3a is prevalence of stunting at 18 months of age that is defined using cut-offs for height/age Z score (HAZ), the model will be as follows:

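### The text of D.2.2.4 stops maternal blood sampling at delivery, contradicting Table 5 and hypothesis 1, which need it at 1 and 3 months; D.4.2 also names two infant outcomes that are not collected

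*Protocol*

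**What the plan says.** **Maternal blood.** Hypothesis 1 (Specific Aims and D.1.1) predicts "higher DHA concentrations in breast milk and blood at 1 and 3 months post-partum" in the supplemented women. In Table 5 the row "Maternal PUFA status" is marked at baseline, birth, 1 month and 3 months. Table 3 gives maternal blood an effect size of 0.50 in its postnatal columns as well as at birth. D.2.2.4, which describes the sampling, says: "Maternal blood samples (7 ml) will be obtained by venipuncture at recruitment and at delivery".

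**Infant blood.** D.2.2.4 takes cord blood at delivery and then: "A 5 ml venous blood sample will be obtained at 3, 12 and 18 months of age from infants". Table 5 shows the same ages (birth, 3, 12 and 18 months), and hypothesis 4 is stated at 3, 12 and 18 months. In D.4.2, however, "infant PUFA status at 1 and 3 months of age will also be examined", and the worked example for aims 1 and 4 is that "breast milk PUFA levels and infant PUFA status at 1 month of age will be higher in the intervention group".

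**Infant skinfolds.** D.4.2 includes skinfold thickness with child growth at 18 months among the principal outcomes. For infants, D.2.2.2 says: "Length, weight and head circumference of the infants will be measured at birth and at 1, 3, 6, 9, 12 and 18 months". The skinfolds in D.2.2.2 are maternal, taken at recruitment.

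**The concern.** Hypotheses, collection schedule, sampling procedure and analysis plan should describe the same data, and here they do not. The maternal item matters most because it could lose data. D.2.2.4 sets out the infant draws age by age in the same paragraph, so its maternal sentence reads as a full list. A team working from it would collect no maternal blood after delivery, and plasma not drawn at 1 and 3 months cannot be obtained later.

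The two D.4.2 items are of another kind. An analyst following that text would look for a 1-month infant blood result and an 18-month skinfold measurement for which the protocol makes no provision. No sample that a hypothesis needs is lost.

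**Working it through.** The check is mainly a comparison of sections.

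| Outcome | Hypotheses | Table 5 | Measurement text | D.4.2 |
|---|---|---|---|---|
| Maternal blood DHA, 1 and 3 months | Yes (hypothesis 1) | Yes | No (D.2.2.4: recruitment and delivery only) | Covered generically, through models for aims 1 and 4 |
| Infant PUFA, 1 month | No | No | No (D.2.2.4) | Yes, named twice |
| Infant PUFA, 3 months | Yes (hypothesis 4) | Yes | Yes | Yes |
| Infant PUFA, 12 and 18 months | Yes (hypothesis 4) | Yes | Yes | Not named; covered generically |
| Infant skinfolds, 18 months | No | No separate row (infant anthropometry is generic) | No (D.2.2.2) | Yes, as a principal outcome |

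**Maternal blood.** Hypothesis 1 and Table 5 agree with each other, and Table 3 attaches a postnatal effect size to maternal blood. D.2.2.4 stands alone against them. D.2.2.5 gives 1 and 3 months for breast milk, in the same subsample of women who give venous blood, but no methods text gives those times for maternal blood.

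**What is at stake in numbers.** The biochemical subsample is 120 pairs per group (D.1.4), so 2 × 120 = 240 women. With two post-partum ages, 240 × 2 = 480 planned maternal samples depend on which section is followed. These are planned numbers, before any loss to follow-up.

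**Power, for context.** D.1.4 claims 95% power for 0.5 SD with 120 per group, two-sided 0.05.

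- Required n per group = 2(1.960 + 1.645)² / 0.5² = 2 × 12.996 / 0.25 ≈ 104. The t-test version gives 105, which is the Table 4 entry.
- At 120 per group, 0.5 × √(120/2) − 1.960 = 3.873 − 1.960 = 1.913, so power is about 0.97.

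The claim holds if read as at least 95%. The power figure is therefore not in dispute. It applies to post-partum maternal blood only if that blood is drawn.

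**Infant PUFA and skinfolds.** At 1 month the number of infant blood samples is 0 under every section that describes collection. For skinfolds, D.2.2.2 provides for 0 infant measurements. Hypothesis 3a and Table 3 do not use infant skinfolds, so no hypothesis or sample-size statement rests on them.

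**Likely origin (an inference).** D.2.2.2 and D.2.2.4 are marked as revised, while D.4 is marked as unchanged. The analysis section may not have been updated with the measurement sections.

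**The case against.** The strongest reply is that Table 5 governs. D.2.1 names it as the place where the data collection details are shown, and E.2 refers to it again for the time points. On that view the maternal draws are planned, and one sentence in D.2.2.4 is incomplete. This stands in part. A reader might infer from D.2.2.4 that post-partum maternal blood is simply not planned, or that D.2.2.4 is the text staff would work from. The documents support neither. What remains is that two current sections give different draw times for the same samples, and the error cannot be repaired if the shorter list is followed. Even then, breast milk at 1 and 3 months and maternal blood at delivery would still be collected.

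A reader might also infer from D.4.2 that hypothesis 4 would go untested at 12 and 18 months. That goes too far. D.4.2 says similar models can be used for aims 1 and 4, and the 1-month case is given there as an example. The later ages are unnamed, not excluded, and their samples are collected. The 1-month label is still wrong, and it occurs twice.

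Finally, the skinfold phrase stands in a sentence with unbalanced parentheses and looks like a stray entry. That is fair, but as written it is a principal outcome with no stated infant measurement.

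**Conclusion.** The point holds as an internal contradiction. D.2.2.4 limits maternal blood to recruitment and delivery, while Table 5 and hypothesis 1 require it at 1 and 3 months post-partum as well. The consequence is conditional: if D.2.2.4 were followed over Table 5, the blood part of hypothesis 1 would have no data in up to 240 women at either age, with no later remedy. If Table 5 is followed, nothing is lost.

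The infant PUFA and skinfold items are secondary. They are errors in the analysis text, affect no sample that a hypothesis needs, and can be corrected without loss of planned data. The skinfold item assumes that the generic infant anthropometry row in Table 5 means the three measures listed in D.2.2.2. The randomised comparisons of growth and development are not affected by any of the three.

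**What to change.** Before enrolment:

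1. Amend D.2.2.4 to list the maternal draws shown in Table 5: recruitment, delivery, and 1 and 3 months post-partum, in the same subsample.
2. In D.4.2, replace infant PUFA at 1 month, in both the outcome list and the worked example, with the ages collected: cord blood at birth, then 3, 12 and 18 months, in line with hypothesis 4, D.2.2.4 and Table 5. Keep 1 month for breast milk, which is sampled then.
3. Reconcile skinfold thickness between D.4.2 and D.2.2.2. Deleting it from the principal outcomes is simplest, since no hypothesis uses it. If the sponsor wants the outcome, D.2.2.2 must add the infant measurement.

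The cost is mainly editing. The maternal draws are already in Table 5 and fall at visits where the same women give breast milk. Only keeping skinfolds would add a measurement.
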